[22]. For acupuncture, the placebo effect size (mean 0.71 (95% confidence interval 0.53, 0.90)) was higher than the overall effect size for all placebo treatments (0.51 (0.46, 0.55)). As with many treatments, higher patient expectation has been shown to be associated with greater improvements following acupuncture treatment. A pooled analysis of four clinical trials of acupuncture found that after completion of treatment, the odds ratio for response between patients considering acupuncture an effective or highly effective therapy and patients who were more sceptical was 1.67 (95% confidence interval 1.20-2.32)
[23]. The use of “sham needle” acupuncture as a placebo control, whereby needling is performed superficially or at non-acupuncture sites, is controversial given that such a procedure may still produce biological responses and hence may not be truly placebo. Blinding of clinicians administering needle acupuncture is also problematic. Such methodological difficulties can be overcome in trials of laser acupuncture as it is possible to successfully blind both participants and clinicians by using specially designed laser machines
[24].

First described by Zelen in the New England Journal of Medicine in 1979
[25], Zelen design trials are a means of reducing bias by minimizing participant expectations in a treatment trial where the knowledge of the intervention itself may influence the study outcome (Hawthorne effect) in the control group. This is done by enrolling participants into an observational study but covertly randomising participants following their recruitment into a treatment trial (post-randomised consent). The control group remains unaware of the treatment being evaluated
[26]. Such a design has been used successfully in a study comparing a physiotherapy treatment of exercise and knee taping to standard non-physiotherapy treatment in people with predominant patellofemoral OA
[27]. A potential disadvantage of the Zelen design can be a higher crossover rate than a usual RCT which may dilute treatment effects in an intention-to-treat analysis. However, a review of 58 RCTs using the Zelen design found that while most trials (n = 41) experienced some crossover from one group to the other (median crossover = 8.9%, interquartile range 2.6% to 15%) the rate was usually within acceptable limits
[26].

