### Procedure

Figure 
1 depicts the trial protocol. Eligibility of prospective participants was determined over the telephone by an investigator (MK) not involved in assessment or treatment of participants. Ethical approval was obtained from the University of Melbourne Human Research Ethics Committee (HREC No. 0931840). All participants provided written informed consent. Initially, all participants consented to participate in a longitudinal observational natural history study of chronic knee pain, involving assessments at baseline, 12 weeks and 12 months. All assessments, comprised solely of questionnaires, are completed by participants at home and mailed back to the University of Melbourne, where data is entered by a blinded assessor (MK).

Upon receipt of completed baseline questionnaires, an investigator (KN) accessed the computerised covert randomisation schedule to reveal whether the participant was allocated either (i) laser acupuncture (could be either real laser or sham laser but the investigator and participant are blinded to this information); (ii) needle acupuncture or; (iii) no treatment (control group). Participants randomised into the no treatment arm continue as consented in the natural history observational cohort for the 12 month duration of the study and did not undergo (or are made aware of) any intervention as part of the trial. Participants randomised to receive either laser or needle acupuncture were telephoned by an investigator (KN) and offered the opportunity to undergo the allocated intervention and contribute their data to the trial. Participants allocated to the laser groups were informed they may receive either real laser or sham laser and that this has been randomly pre-determined and would not be revealed to them until the completion of the 12 month assessments. Participants willing to participate in the intervention provided informed consent to do so at this point. Participants who choose not to participate in the intervention continued as initially consented in the natural history observational cohort for 12 months, however their data will be analysed as per intention-to-treat.

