### Blinding

Laser and sham laser participants were blinded to treatment allocation, as were the GPs administering laser and sham laser acupuncture, as the same machine provided both interventions and the participant code (entered by the GP) determined whether the machine actually outputted laser or not
[24]. Participants in the no treatment group are unaware that the treatment groups exist and that their data will be used for comparison (despite having consented to their longitudinal data being used for other unspecified research questions as determined by the researchers). Only the participants undergoing needle acupuncture and the GP provider were unblinded to their treatment group allocation.

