### Statistical analyses

The primary analysis of the data will be undertaken using the principle of intention-to-treat with all randomised patients included in the analyses. Demographic and clinical characteristics, as well as baseline data, will be presented to assess the baseline comparability of the intervention groups. Descriptive statistics will be presented for each group as the mean change (standard deviation, 95% confidence intervals) in the outcomes from baseline to each time point. Differences in mean change from baseline to each time point will be compared between groups using random effects linear regression modelling adjusting for baseline levels of the outcome measure and using the treating therapists as random effects to account for clustering of outcomes by therapists. Model assumptions will be checked by standard diagnostic plots. Improvement between acupuncture groups (based on the perceived ratings of change) will be compared using logistic regression with random effects as above and presented as odds ratios with 95% confidence intervals. Multiple imputation methodology will be employed to account for missing data
[51]. No statistical adjustment will be made for multiple testing. All tests will be two sided and carried out at the 5% level of significance.

As part of the secondary analyses of the primary outcomes at 12 weeks and 12 months, we plan to conduct a separate analysis to estimate the effect of treatment in the hypothetical scenario of full adherence to the randomised treatment intervention. Analytical methods for this will utilise instrumental variables methodology involving two stage least squares estimation
[52].

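### The two-stage least squares analysis is labelled as the effect under full adherence, but it estimates the effect among participants who accept the offered treatment

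*Protocol article*

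**What the plan says.** The Statistical analyses section makes the primary analysis one "using the principle of intention-to-treat with all randomised patients included in the analyses". It then adds, "As part of the secondary analyses of the primary outcomes at 12 weeks and 12 months", a separate analysis "to estimate the effect of treatment in the hypothetical scenario of full adherence to the randomised treatment intervention". The method is named: "Analytical methods for this will utilise instrumental variables methodology involving two stage least squares estimation". So both a target and an estimator are given. The section states no assumption linking the two.

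The Procedure section fixes what non-acceptance means. After covert randomisation, people in the acupuncture arms are telephoned and offered their allocated treatment. "Participants who choose not to participate in the intervention continued as initially consented in the natural history observational cohort for 12 months", and their data stay in the intention-to-treat analysis. The no-treatment arm receives no trial intervention and is not told of one. Sample size calculations assumes 15% non-consent in each of the three treatment arms.

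The offers are not all alike. For laser, "Participants allocated to the laser groups were informed they may receive either real laser or sham laser", so real and sham laser share one offer. For needle, the treatment is open: "Only the participants undergoing needle acupuncture and the GP provider were unblinded to their treatment group allocation".

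**The concern.** Non-acceptance here is one-sided: people allocated to treatment can decline it, but controls cannot obtain it from the trial. In that setting an instrumental variables estimate based on randomised arm describes those who would accept the offer. The decliners' response to treatment is never observed, so the data carry no information about it. A statement about full adherence in everyone randomised therefore needs an added assumption that decliners would respond as accepters do.

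The label matters because a Zelen design dilutes the intention-to-treat contrast, and readers may take the adherence-adjusted estimate as the treatment's true effect. It would be given for both primary outcomes at both time points, for a wider population than the method supports.

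Laser versus needle (H3) raises a second issue. The two offers differ, so the people who accept them may differ in number and in kind. The result then depends on how the two-stage model is set up.

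**Working it through.** **Inputs.** From Sample size calculations: 15% non-consent in each treatment arm (acceptance p = 0.85), target difference 1.8 NRS units, SD 3.0, baseline correlation 0.50, 70 per arm, 15% loss to follow-up. Assumed here: decliners' effects, unequal acceptance rates, randomised arm as the instrument, exposure coded as offer accepted or not, and no effect on outcome of an offer that is declined.

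**The plan's own figures.** The section gives no figure for the two-stage analysis. Its dilution factor is 1/(1 − 0.15)² = 1/0.7225 = 1.384, the stated 38%. Then 40/0.7225/0.85 = 65.1, rounded up to the stated 66 per arm. The 38% inflation treats the intention-to-treat effect as 0.85 times the effect in accepters; two-stage least squares reverses that step.

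**Accepters versus full adherence.** With accepter effect C and decliner effect D:

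- Intention-to-treat effect = p × C = 0.85 × 1.8 = 1.53.
- Two-stage estimate = 1.53/0.85 = 1.80, which is C whatever D is.
- Full-adherence effect = p × C + (1 − p) × D.

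| Acceptance p | D = 1.8 | D = 0.9 | D = 0 |
|---|---|---|---|
| 0.95 | 1.80 | 1.76 | 1.71 |
| 0.85 | 1.80 | 1.67 | 1.53 |
| 0.70 | 1.80 | 1.53 | 1.26 |

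At the protocol's 15%, the gap runs from 0 to 1.80 − 1.53 = 0.27 units over this range of D.

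**Laser versus needle, two arms, one exposure (laser received).** Needle accepters and needle decliners both count as not having received laser. With acceptance pL and pN and effects tL and tN, the target is (pL × tL − pN × tN)/pL = tL − (pN/pL) × tN. With tL = tN = 1.8 the true difference is 0, and the fit gives:

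- pL 0.85, pN 0.85: 0.
- pL 0.85, pN 0.75: 1.8 × (1 − 0.75/0.85) = +0.21.
- pL 0.75, pN 0.85: 1.8 × (1 − 0.85/0.75) = −0.24.

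**Laser versus needle, four arms jointly.** Three treatment-received indicators are instrumented by the three arm indicators, with no treatment as reference. In a simulation of 2,000,000 patients with a constant effect of 1.8, the laser-needle difference was +0.01 at 0.85/0.75 and −0.01 at 0.75/0.85. Unequal acceptance alone causes no bias in this form.

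The effect was then allowed to fall with willingness (assumed: 1.8 in the most willing 75%, 0.9 in the next 10%, 0 in the last 15%). At 0.85/0.75 the laser accepters' effect is (0.75 × 1.8 + 0.10 × 0.9)/0.85 = 1.69 and the needle accepters' is 1.80, a difference of −0.11. The simulation gave −0.11, and +0.11 with the rates reversed. Here the two accepter groups are different people.

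**Laser versus sham.** One blinded offer serves both arms, so acceptance is equal in expectation and either form gives the accepters' effect.

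**The case against.** Under a constant treatment effect, calling the estimate a full-adherence effect is correct. The section cites a methods source that is not available here, and that source or a separate analysis plan may state the assumption. This stands in part: the remedy can be as small as one sentence. But the article names its own target and its own method, and the second does not deliver the first without that sentence.

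A reader might infer that the laser-needle comparison is biased whenever the two offers are accepted at different rates. The document does not support that. Such bias needs a two-arm, single-exposure fit, which the section does not specify; a joint fit is equally compatible with it. The plan also assumes the same 15% non-consent in every treatment arm, the 10-point gaps above are invented, and their sign reverses with the direction of the gap. Leaving exposure coding to an analysis plan is no fault in an article.

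A reader might also infer that the protocol itself shows decliners would benefit less, because the Background says "higher patient expectation has been shown to be associated with greater improvements following acupuncture treatment" (odds ratio 1.67). That figure compares believers with sceptics among people in acupuncture trials. It does not show that decliners are the sceptics, nor how much they would gain relative to control. People may decline for other reasons, such as the 8 to 12 visits required. The evidence makes equal effects open to doubt and goes no further.

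Adherence is measured in the article as sessions attended, so the exposure may not be binary acceptance. The arithmetic above covers only the binary form. A session-based exposure would need its own assumption, which again is not stated.

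Finally, the sizes are modest. The standard error of the two-stage estimate, ignoring clustering, is about 3.0 × √(1 − 0.50²) × √(2/(70 × 0.85))/0.85 = 0.476/0.85 = 0.56 units. Every gap shown at 15% non-consent, and each two-arm bias listed, is below half of that. This stands, and it limits the weight of the point.

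**Conclusion.** The point holds as a mismatch between the stated target and the named method. The analysis gives the effect in accepters. At 15% non-consent and an accepter effect of 1.8 NRS units, it exceeds the full-adherence effect by 0 to 0.27 units as the decliners' assumed effect goes from 1.8 to 0. This rests on randomised arm as instrument, acceptance as exposure, and a declined offer having no effect of its own.

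For laser versus needle the conclusion is conditional. A two-arm, single-exposure fit would mislead by about 0.2 units for a 10-point acceptance gap; a joint fit would not under a constant effect, and could differ by about 0.1 under the varying effects assumed here. No bias in the planned analysis is shown, because the form of the fit is not stated.

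The correction is worth making because it governs what a secondary analysis of both primary outcomes may conclude. The intention-to-treat analysis and the sample size are untouched.

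**What to change.** Name the estimand as the effect among participants who accept the offered treatment (complier average causal effect) and limit the conclusion to them. If the full-adherence wording is kept, state beside it the assumption that decliners would benefit as much as accepters, and show how the result moves if they would not.

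For laser versus needle, fit all four arms in one two-stage model: real laser, sham laser and needle received as the exposures, randomised arm as the instruments, no treatment as reference. Derive the laser-needle difference from that model. Report acceptance by arm, and note that laser and needle accepters may be different groups even if the rates agree.

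The cost is a few lines of wording and one joint model. The no-treatment arm that it needs already exists. The price is a narrower secondary claim.

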### Economic evaluation

The economic evaluation will be conducted from the perspective of the Australian health care system and the individual patient. Standard methods of economic evaluation alongside a clinical trial will be used to evaluate the differences in resource use and health outcomes at the end of treatment and at 12 months. The primary economic evaluation will take the form of a cost effectiveness study with a range of outcome measures including the incremental cost per extra person with a clinically significant improvement in pain and function and per extra quality adjusted life years (QALYs) for laser acupuncture compared to either sham or needle acupuncture. The difference in QALYs will be calculated in the primary analysis as the difference in the area under the curve for AQoL scores over the duration of 12 months. Differences in mean change from baseline for the AQoL to each time point will be weighted by the time from baseline using generalised linear regression modelling adjusting for baseline levels of the AQoL to construct QALYs, and then compared between groups. Differences in the mean cost between groups will be calculated using generalised linear regression modelling. Incremental cost per QALY will be calculated as the ratio of the difference in mean cost to the difference in mean QALYs with 95% confidence intervals calculated using Fieller's theorem.

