**Methods/Design:**

Two hundred and eighty two people aged over 50 years with chronic knee pain have been recruited from metropolitan Melbourne and regional Victoria, Australia. Participants originally consented to participate in a longitudinal natural history study but were then covertly randomised into one of four treatment groups. One group continued as originally consented (ie natural history group) and received no acupuncture treatment. The other three were treatment groups: i) laser acupuncture, ii) sham laser or, iii) needle acupuncture. Acupuncture treatments used a combined Western and Traditional Chinese Medicine style, were delivered by general practitioners and comprised 8–12 visits over 12 weeks. Follow-up is currently ongoing. The primary outcomes are pain measured by an 11-point numeric rating scale (NRS) and self-reported physical function measured by the Western Ontario and McMaster (WOMAC) Universities Osteoarthritis Index subscale at the completion of treatment at 12 weeks. Secondary outcomes include quality of life, global rating of change scores and additional measures of pain (other NRS and WOMAC subscale) and physical function (NRS). Additional parameters include a range of psychosocial measures in order to evaluate potential relationships with acupuncture treatment outcomes. Relative cost-effectiveness will be determined from health service usage and outcome data. Follow-up assessments will also occur at 12 months.

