**Discussion:**

The findings from this study will help determine whether laser and/or needle acupuncture is efficacious, and cost-effective, in the management of chronic knee pain in older people.

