Thus, we are currently conducting a Zelen design RCT to investigate the efficacy of needle and laser acupuncture administered by experienced medical acupuncturists in people with chronic knee pain and to evaluate maintenance of effects over the longer term. We will also evaluate the cost-effectiveness of needle and laser acupuncture, as well as explore whether psychosocial measures are associated with changes in pain, physical function and health-related quality of life following acupuncture treatment. This paper describes the protocol for this ongoing trial.

The primary hypotheses are that:

H1: Laser acupuncture will result in significantly greater improvements in pain (as measured overall via numerical rating scale (NRS)) and physical function (as measured via Western Ontario and McMaster (WOMAC) Universities Osteoarthritis Index) than sham laser acupuncture at 12 weeks.

H2: Laser and needle acupuncture will result in significantly greater improvements in pain (as measured overall via NRS and physical function (as measured via WOMAC) than no treatment at 12 weeks.

H3: Laser acupuncture will result in significantly greater improvements in pain (as measured overall via NRS) and physical function (as measured via WOMAC) than needle acupuncture at 12 weeks.

The secondary hypotheses are that:

H4: Sham laser acupuncture will result in significantly greater improvements in pain (as measured overall via NRS) and physical function (as measured via WOMAC) than no treatment at 12 weeks.

H5: Laser, sham laser and needle acupuncture will result in significantly greater improvements in pain (as measured overall via NRS) and physical function (as measured via WOMAC) than no treatment at 12 months, while laser acupuncture will result in significantly greater improvements than needle acupuncture.

H6: Laser, sham laser and needle acupuncture will result in significantly greater improvements in pain (as measured on standing and walking via NRS and by WOMAC), physical function (as measured via NRS) and health-related quality of life than no treatment at 12 weeks and 12 months.

H7: Laser acupuncture will result in significantly greater improvements in pain (as measured on standing and walking via NRS and by WOMAC), physical function (as measured via NRS) and health-related quality of life than needle acupuncture at 12 weeks and 12 months.

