### Randomisation and allocation concealment

The randomisation schedule was prepared by the study biostatistician (AF). All eligible participants were consecutively randomised into either the (i) real laser acupuncture; (ii) sham laser acupuncture; (iii) needle acupuncture or; (iv) no treatment group. Allocation was randomised within random permuted blocks of six to twelve generated a priori and stratified according to treating GP so that all GPs delivered approximately equal numbers in each acupuncture group to control for therapist variation. An electronic password-protected spreadsheet that contained concealed acupuncture group allocation was prepared by a researcher (BM) with no other involvement in the study, and held by an investigator (MP) not involved in recruitment, assessment or treatment. The patient code numbers for the randomised laser treatment arms were entered into the study laser machines by an independent biomedical engineer, in order to permit blinding of both the treating GPs and the participants.

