Acupuncture treatments (approximately 20 minutes in duration) were administered once or twice weekly (at the GP’s discretion) in the GP’s rooms for 12 weeks, with a minimum of 8 and a maximum of 12 treatments delivered. Participants did not pay for treatment and the treating GPs were reimbursed for their time on a per patient basis.

The treatment protocol permitted the GPs to treat participants as they would treat patients in their normal practice. They were allowed to select from a standardized set of acupuncture points around the knee, as well as distal points on the intervention side (Table 
2). Other points could be used at the GP’s discretion depending on the cause(s) and site of the pain evident at clinical examination. These included points indicated by Traditional Chinese Medicine diagnoses in relation to Zang-Fu organ dysfunction, associated meridian and deep channel connections and ear points. Because of varying participant sensitivity, the initial treatment session permitted a maximum of six points in total, including four points on the study limb and two other points chosen as per protocol. In subsequent treatment sessions, further points were added as clinically indicated by participant response to treatment, as well as local tenderness, muscle tightness and/or swelling. Over subsequent treatments, acupuncture points were varied according to changes in participant symptoms and point reactivity. The 12-week treatment period allowed for patient attendance flexibility (a break of up to four weeks between visits was deemed acceptable for participants going away on holidays etc.), as well as for strong acupuncture responders to have several days settling time as necessary. Visits were scheduled twice per week if necessary, but weekly visits were generally recommended. Treatment was considered complete when pain and function had returned to normal, however a minimum of 8 treatments was required. Laser acupuncture interventions were administered with the patient positioned either supine or sitting over the edge of the treatment couch. Treating GPs completed standardized treatment notes after each acupuncture session. Information recorded included the acupuncture points treated and any adverse events reported by the patient from the previous session.

**Table 2 T2:** Framework of acupuncture points that could be selected by general practitioners when administering acupuncture treatments (laser and needles)

**Location**	**Acupuncture points**

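### The primary cost-effectiveness ratios compare laser only with sham and with needle, so none of them shows whether offering either treatment is worth its cost against no acupuncture

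*Protocol article*

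**What the plan says.** The Economic evaluation section sets out the primary analysis: "The primary economic evaluation will take the form of a cost effectiveness study with a range of outcome measures". The measures listed are the incremental cost per extra person with a clinically significant improvement and the incremental cost "per extra quality adjusted life years (QALYs) for laser acupuncture compared to either sham or needle acupuncture". Later sentences in that section compare QALYs and mean costs between groups without naming any further pair of arms.

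The aims are wider. The Background says "We will also evaluate the cost-effectiveness of needle and laser acupuncture". The Discussion paragraph of the abstract says the findings will help determine "whether laser and/or needle acupuncture is efficacious, and cost-effective, in the management of chronic knee pain in older people". The Methods/Design paragraph of the abstract is narrower: "Relative cost-effectiveness will be determined from health service usage and outcome data".

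On the arms, the abstract says of the fourth group: "One group continued as originally consented (ie natural history group) and received no acupuncture treatment". The Interventions section gives the acupuncture course as 12 weeks "with a minimum of 8 and a maximum of 12 treatments delivered", without distinguishing the three acupuncture arms. Randomisation was "stratified according to treating GP so that all GPs delivered approximately equal numbers in each acupuncture group to control for therapist variation". The Blinding section says laser and sham were delivered by the same machine.

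**The concern.** Whether a treatment is cost-effective depends on what it is compared with. For a payer or patient deciding whether acupuncture should be offered at all, the comparator is not offering it, and this trial has a randomised arm for that. Primary hypothesis H2 already uses that arm for pain and function. The economic section does not name it. Needle acupuncture appears there only as a comparator for laser.

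The cost of the acupuncture visits is common to laser, sham and needle, so the named ratios are largely insensitive to it. Suppose laser and needle were equally good or equally poor value against no treatment: the laser versus needle ratio would look much the same in both cases. Laser versus sham isolates the effect of the beam, but a small incremental cost there could be misread as showing that laser acupuncture is cheap to provide.

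**Working it through.** **The plan's own figures.** The Economic evaluation section gives no number to reproduce. The one planning figure used below is the 15% non-consent rate from Sample size calculations. It is used there as 1/(1 − 0.15)² = 1/0.7225 = 1.384, which matches the stated 38% inflation. Then 40 × 1.384 = 55.4, rounded up to 56, and 56/0.85 = 65.9, rounded up to the stated 66 per arm.

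**Inputs.**
- Visits per treated patient: v = 8 to 12 in each acupuncture arm (Interventions).
- Uptake: u = 1 − 0.15 = 0.85, taken as equal in the three acupuncture arms (Sample size calculations). Decliners stay in their randomised arm for analysis (Procedure).
- Visits in the no-treatment arm: 0 (abstract).
- Unit cost per visit: c. The documents give no value, so it is left as a symbol.

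**Visit cost per randomised patient.** In an acupuncture arm it is u × v × c. In the no-treatment arm it is 0.

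| Comparison | Visit-cost difference per randomised patient |
|---|---|
| Laser − sham, equal attendance | 0.85 × (v − v) × c = 0 |
| Laser − needle, equal attendance | 0.85 × (v − v) × c = 0 |
| Laser − needle, mean attendance differing by one visit | 0.85 × 1 × c = 0.85c |
| Laser or needle − no treatment, 8 visits | 0.85 × 8 × c = 6.8c |
| Laser or needle − no treatment, 12 visits | 0.85 × 12 × c = 10.2c |

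On the two named comparisons, c drops out at equal attendance: doubling or halving the price of a visit changes neither ratio. Needle and device costs, and any difference in other health-care use, remain. Against no treatment, the same c is multiplied by 6.8 to 10.2.

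**Are the data there?** The Outcome measures section says most outcomes are measured at all three time points in every participant, whatever the allocation. Table 3 lists the AQoL and the health-care log-book at baseline, 12 weeks and 12 months. It also lists session attendance from GP treatment records. The log-book looks back only four weeks, so those records are the natural source for counting study visits. Interventions says participants did not pay and GPs were reimbursed, so the visits will enter the analysis only if a unit cost is deliberately assigned to them.

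**The case against.** The strongest reply is that the sentence describes only the primary economic evaluation. The section also promises standard methods and comparisons between groups, and a condensed article may leave secondary contrasts to a fuller plan. A comparison with no treatment is indeed not ruled out. But the article states a choice of comparators and names no other. The open-ended wording in that sentence widens the list of outcome measures, not the list of arms. As written, the primary evaluation does not match the aims in the Background and abstract.

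Other parts of the reply stand, and they rule out stronger readings that a reader might infer:

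- **That neither treatment's cost-effectiveness is estimated at all.** Laser versus needle is a legitimate ratio between two real treatments, and the abstract's methods speak of relative cost-effectiveness. What is missing is the comparison with no acupuncture.
- **That laser versus sham has near-zero incremental cost by construction.** Only the scheduled visit cost cancels, and only at similar attendance. Treatment could end once symptoms had resolved, subject to the minimum, so visit numbers may vary with response. The log-book captures hospital, practitioner, drug and home-assistance use, which may differ between arms.
- **That the planned ratios are understated by some sum per QALY.** The documents give neither a visit price nor a QALY gain. Changing the comparator also changes the QALY difference, so the ratio against no treatment is a different quantity, not a corrected version of the same one.
- **That sham must be removed.** Keeping it is a matter of preference, provided it is interpreted correctly.

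None of H1 to H9 concerns costs, so the efficacy analyses are unaffected.

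**Conclusion.** The point holds in this form: the primary economic comparators do not match the stated aim of determining whether laser and needle acupuncture are cost-effective. No named ratio sets either treatment against no acupuncture. The resource that largely drops out of the named comparisons is about 6.8 to 10.2 GP visits per randomised patient.

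That range assumes 85% uptake, 8 to 12 visits for everyone who accepts, and no study visits in the control arm. At full uptake it would be 8 to 12; early drop-out would lower it. The cancellation assumes similar attendance across the acupuncture arms and does not extend to needle, device or other health-care costs. No currency amount can be attached from the documents. The consequence is confined to the economic aim, but on that aim the plan as written leaves the main question unanswered.

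**What to change.** In the Economic evaluation section:

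1. Add laser versus no treatment and needle versus no treatment as named economic comparisons, each as cost per extra responder and cost per QALY, by intention-to-treat.
2. State that the GP acupuncture visits are costed, with visit numbers from the GP treatment records and a declared unit cost.
3. Keep laser versus needle as the incremental step between the two active treatments.
4. If laser versus sham stays, say that it concerns the effect of the laser output and is not to be read as the cost-effectiveness of providing laser acupuncture.

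The cost is two more contrasts and a few sentences. The control arm's outcome and resource-use data are already being collected, so no change to recruitment or follow-up is needed. The article describes follow-up as still under way, so the change can be made before the analysis.
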